### **13.2 Statistical and analytical plan**

The primary outcome (DAOH-D90) and other non-parametric outcomes will be analysed using quantile regression with results presented as median difference (95%CI). Mortality and other binomial outcomes will be analysed using logistic regression with results reported as odds ratios (95%CI). Time to event outcomes will be analysed using proportional hazards regression with results presented as Kaplan Meier or cumulative incidence curves where mortality is a competing risk. Functional status and quality of life will employ longitudinal analysis techniques to account for data collected at both 6 and 12 months. All analyses will account for site with participants nested within site and site treated as a random effect. Where baseline imbalance ( $p < 0.2$ ) is observed between treatment arms, sensitivity analysis will be performed adjusting for imbalanced variables. Sensitivity to missingness will be performed using multiple imputation. A secondary analysis will be conducted using a Bayesian approach to model a posterior probability of the odds ratio for days alive and out of hospital at 90

days post-randomisation between the intervention and control group with associated 95% credible interval (CrI). Statistical analysis will be performed using SAS or R and a detailed statistical analysis plan will be published or posted in the public domain prior to study completion.

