### **Validity of trial primary outcome**

Septic shock is associated with significant mortality and reduced quality of life in survivors. The primary outcome of days alive and out of hospital to day 90 (DAOH-D90) is a patient-centred outcome measure that will capture both death and morbidity. DAOH has been validated in other settings where mortality alone is insufficient to capture the burden of disease, particularly the longer term functional outcome sequelae [34, 35]. The choice of DAOH-D90 was informed by extensive consumer consultation with time spent out of hospital and at home considered to be an important outcome. DAOH is readily quantifiable and is currently being used as an outcome measure in another critical care trial [36]. A between group difference of 7 days in DAOH-D90 was informed by data from the ARISE randomised clinical trial and the ARISE FLUIDS observational study and is considered to be biologically plausible, clinically meaningful and important to sepsis survivors. In addition to capturing the overall burden of disease both in hospital and after discharge, a 7-day reduction in DAOH-D90 will have significant resource and cost implications.

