## 8. STUDY OUTCOME MEASURES

### 8.1 Primary outcome

The primary study outcome is the number of days alive out of hospital at 90 days post randomisation (DAOH-D 90). Participants who die on or prior to day 90 will be assigned zero days alive and out of hospital.

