### **13.1 Sample size calculation**

Based on the data from the ARISE trial [10], the mean (standard deviation) of DAOH-D90 was 60(31). Assuming a clinically important increase of 7 days in the vasopressors arm, a sample size of 950 will have 90% power to detect this difference with a type I error rate of 0.05 (including a 15% inflation factor to account for the non-parametric distribution). Allowing for a 5% drop out rate, we will recruit 1000 participants to the trial. A 7 day difference in DAOH-D90 is considered clinically important and is supported by consumers.

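### The trial is sized on mean DAOH-D90 but its primary result is a median difference, which gives a death no more weight than any below-median survivor and can disagree in direction with the mean

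*Protocol*

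**What the plan says.** Section 8.1 sets the scoring of deaths: "Participants who die on or prior to day 90 will be assigned zero days alive and out of hospital". Section 6, under the validity of the primary outcome, says that DAOH-D90 "is a patient-centred outcome measure that will capture both death and morbidity".

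Section 13.1 plans on means. It takes from an earlier trial that "the mean (standard deviation) of DAOH-D90 was 60(31"). The target is a gain of 7 days with the vasopressor strategy, and the section states that "a sample size of 950 will have 90% power to detect this difference with a type I error rate of 0.05". That total already contains a 15% allowance for non-normality.

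Section 13.2 analyses on medians: "The primary outcome (DAOH-D90) and other non-parametric outcomes will be analysed using quantile regression with results presented as median difference (95%CI"). It names no mean difference for DAOH-D90 and does not say how a median difference that conflicts with mortality would be presented. It does list a secondary Bayesian analysis that yields an odds ratio for DAOH-D90. Section 8.2 makes 90-day all-cause mortality and time to death the first two secondary outcomes.

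**The concern.** A score of zero for death is meant to let one number balance survival against time in hospital. The mean does this: each death costs that arm the whole of a survivor's days. The median registers only which side of it a patient falls on. With mortality well under 50%, a patient who died and a survivor with a slightly longer stay than the median patient count the same.

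The two summaries can therefore separate when a strategy changes deaths and survivor stays in opposite directions. The headline days-alive result could then favour the arm with more deaths, although that arm has fewer mean days alive out of hospital, and the mean is the quantity on which the trial was planned.

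**Working it through.** **Inputs from the protocol.** Mean 60, SD 31, difference 7 days, 90% power, type I error 0.05, 15% inflation, 5% drop-out (13.1); deaths scored 0 (8.1); 1:1 allocation (10.1). In-hospital mortality is given as 18% for ICU sepsis, 22% with shock, and 8% in the investigators' own observational study (section 6).

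**The plan's own figure.** Two-sided test (an assumption; sidedness is not stated):

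n per arm = 2 × (1.960 + 1.282)² × 31² / 7² = 412.1, so 413 per arm and 826 in total.
826 × 1.15 = 949.9 (stated 950). 950 / 0.95 = 1000 (stated 1000).

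The sample size reproduces, and it is a comparison of means.

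**Illustrative model (assumptions).** DAOH-D90 is 0 with probability m; otherwise it is 90 minus a lognormal number of hospital days, capped at 90. For each m the lognormal is solved so that the overall mean is 60 and the SD 31. Zero scoring with these figures requires 1 − m ≥ 60² / (60² + 31²) = 3600 / 4561 = 0.789, so m is at most about 21%. The 22% rate cannot serve as the base. At m = 0.18 the solution is a median stay of 12.5 days with sigma 0.785.

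**More deaths, stays unchanged (18% to 23%).**

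- Mean: survivors average 60 / 0.82 = 73.17 days. 0.77 × 73.17 = 56.34, a fall of 3.7 days.
- Median: solve m + (1 − m) × P(survivor days ≤ t) = 0.5.
  - At 18%: (0.5 − 0.18) / 0.82 = 0.390, and t = 90 − 12.49 × exp(0.785 × 0.279) = 74.4.
  - At 23%: (0.5 − 0.23) / 0.77 = 0.351, and t = 90 − 12.49 × exp(0.785 × 0.384) = 73.1, a fall of 1.3 days.

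**More deaths with shorter survivor stays.** With stays 20% shorter, the median at 23% deaths is 90 − 0.8 × 16.88 = 76.5, up 2.0 days. Mean survivor stay falls from 16.83 to about 13.46 days, so the overall mean is 0.77 × 76.54 = 58.9, down 1.1 days. Differences for the arm with 5 points more deaths are:

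| Control mortality | Stays shorter by | Mean difference | Median difference | 95% CI favours arm with more deaths |
|---|---|---|---|---|
| 18% | 10% | −2.4 | +0.3 | about 2% |
| 18% | 20% | −1.1 | +2.0 | about 22% |
| 18% | 25% | −0.5 | +2.9 | about 49% |
| 18% | 30% | +0.2 | +3.7 | not run |
| 15% | 20% | −0.7 | +1.9 | about 14% |
| 15% | 25% | +0.05 | +2.8 | not run |
| 20% | 20% | −1.5 | +2.3 | about 48% |
| 8% | 20% | +0.02 | +1.8 | not run |

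The last column comes from 1,000 simulated trials per row, 475 per arm, with bootstrap percentile intervals for the median difference. It counts trials by the true mean difference. Trials in which the observed mean was also lower are fewer: about 7% and 17% for the 20% and 25% rows at 18% mortality.

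**A second survivor shape.** With a Beta distribution for survivors, also fitted to mean 60 and SD 31, take 18% against 24% deaths and a 5-day survivor gain capped at 88 days. Means are 59.9 and 58.5; medians are 73 and 75. Quantile regression was significant towards the arm with more deaths in 35% of 400 trials, and significant with a lower observed mean in 16%. The reversal does not depend on one distribution.

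**The case against.** A reader might infer that the zero assigned to deaths has no effect on the primary analysis. That does not hold. Every death is an observation below the median, so 5 points more deaths alone lowers the median by 1.3 days. The rule also matters for deaths after discharge: in the Beta model, if 5% to 20% of deaths would otherwise have had days above the median, scoring them 0 lowers the median by about 0.5 to 1.9 days. What the median ignores is only how far below it a death is scored.

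The reversal also needs two opposing effects in one arm, and nothing in the protocol predicts them. At 10% shorter stays it is rare. At the 8% mortality of the observational study, with 20% shorter stays, the mean does not fall. This stands, and it limits the point to a possible outcome.

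Nor does the mean remove every conflict with mortality: at 18% mortality and 30% shorter stays it too favours the arm with more deaths (+0.2 days). This also stands, and it is why mortality belongs beside both summaries.

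Mortality and time to death are already secondary outcomes, and an odds ratio for DAOH-D90 is planned. A conflict with mortality would be visible. But none of these gives the difference in days on the scale used in 13.1.

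Finally, supplementary analyses are often left to the SAP. That is fair for the detail, and if the SAP already specifies the mean difference the point is answered. The mismatch itself is in the protocol, which fixes a mean for planning and a median for the primary result.

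**Conclusion.** The point holds in limited form. The primary summary is a different parameter from the one planned, and it responds less to deaths: 1.3 days against 3.7 for 5 points more mortality in the model at 18%. When more deaths coincide with 20% to 25% shorter survivor stays, the median difference can favour the arm with more deaths while its mean is 0.5 to 1.1 days lower, with a CI excluding zero in about 22% to 49% of trials.

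These figures rest on assumed mortality, assumed opposing effects, and assumed survivor shapes fitted to mean 60 and SD 31, taking deaths as scored 0 in the source data. They are illustrations, not forecasts. A reader might infer that quantile regression is the wrong method or that the sample-size arithmetic is wrong. Neither follows: a median is a legitimate summary of a skewed outcome, and 950 and 1000 reproduce.

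**What to change.** Keep the outcome, the scoring of deaths and the quantile regression. Add to section 13.2: the difference in mean DAOH-D90 between arms, with deaths scored 0, will be estimated with a site-stratified bootstrap 95% CI and reported beside the median difference and 90-day mortality; any disagreement in direction among the three will be stated in the primary report.

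Do not make agreement of all three point estimates a condition for claiming benefit. In simulations with 18% mortality, 30% shorter stays and no mortality effect, such a rule cut power from about 97% to between 53% and 59% in two runs. Section 6 needs no rewriting.

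The cost is one extra analysis of data already held, and the possibility that a positive median result must be presented with a conflicting mean. It should be fixed before results are known.

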## 6. BACKGROUND AND RATIONALE

### Sepsis is a major public health problem

Identified as a Global Health Priority by the World Health Organisation [1], sepsis (defined as life-threatening organ dysfunction due to a dysregulated host response to infection) is estimated to affect 50 million people worldwide each year [2]. In industrialised countries, it accounts for significant mortality, morbidity, and healthcare expenditure [3]. The Australian Sepsis Network reports an annual incidence of sepsis requiring admission to an Intensive Care Unit (ICU) of 0.77/1000, approximately 18,000 cases, with an estimated cost per episode of \$39,000 [4]. Data from the Australian and New Zealand Intensive Care Society (ANZICS) have shown that sepsis accounts for 11% of all ICU admissions, with an overall in-hospital mortality rate of 18%, and 22% in the subgroup with shock [5]. As mortality has fallen in the past two decades there is increasing awareness of the burden of morbidity among survivors [6]. One third of those treated in an ICU for sepsis have not returned to their previous level of function by six months [7].

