### **Preliminary data and feasibility**

We recently completed an observational study of initial sepsis resuscitation practices in 70 hospitals in Australia and New Zealand (n=591) [29]. Among those with septic shock (n=82), in-hospital mortality was 8% (95% CI 3-

15%). A median volume of 4.8 L (IQR 3.9-6.2 L) was given in the first 24 hours. The fluid volume prior to commencing vasopressors was 2 L (IQR 1.2-3.0 L). Even accounting for confounders such as source of infection, age and comorbidity, this study demonstrates considerable variation in usual care and scope to undertake a trial comparing a smaller initial volume of fluid combined with earlier vasopressor use to a larger initial volume and later vasopressor administration to restore systemic arterial blood pressure in patients with early septic shock.

A vasopressor infusion conventionally requires insertion of a central venous catheter (CVC). In the ARISE trial, 40% of patients initially commenced vasopressors via a peripheral IV catheter prior to CVC insertion [30], particularly for sicker patients with shock [31]. We performed a systematic review which verified the safety of this approach [32]. Accordingly, initial peripheral vasopressor administration in our trial will facilitate earlier introduction and avoid unnecessary CVC insertion where vasopressors are required for only a short period of time.

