### 8.2 Secondary outcomes

1. All-cause mortality at 90 days
2. Time from randomisation until death (to day 90)
3. Days alive and at home at 90 days post-randomisation
4. Ventilator-free days to day 28
5. Vasopressor-free days to day 28
6. Renal replacement therapy-free days to day 28
7. Death or disability at 6 and 12 months\*

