### 8.3 Tertiary outcomes

1. Incidence and duration of invasive mechanical ventilation
2. Incidence and duration of vasopressor support
3. Incidence and duration of acute renal replacement therapy
4. ED length of stay
5. ICU length of stay
6. Hospital length of stay
7. In hospital mortality (censored at 90 days)

8. Mortality at 6 and 12 months\*
9. Quality of life at 6 and 12 months\*
10. Cost-effectiveness measured as cost/QALY\*

\*May be reported separately when 12-month follow up complete

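### A median difference is the prescribed summary for 28-day free-day outcomes: it cannot respond for renal-replacement-free days, and may not for ventilator-free days

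*Protocol*

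**What the plan says.** Section 13.2 sorts outcomes by type. The primary outcome "and other non-parametric outcomes will be analysed using quantile regression with results presented as median difference (95%CI"). Binomial outcomes go to logistic regression, time-to-event outcomes to proportional hazards regression, and functional status and quality of life to longitudinal methods. All analyses treat site as a random effect.

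Section 8.2 lists, among seven secondary outcomes, "Ventilator-free days to day 28", the matching count for vasopressors, and "Renal replacement therapy-free days to day 28". Section 13.2 does not name them. They are bounded day counts and fit none of the other three groups, so the quantile-regression rule is the only one in the text that can apply to them.

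The protocol does not say how these three counts are scored. Its only scoring rule for death concerns the primary outcome, in section 8.1: "Participants who die on or prior to day 90 will be assigned zero days alive and out of hospital". It gives no expected rate of ventilation or renal replacement. Section 8.3 lists the incidence and duration of each support as tertiary outcomes, for example "Incidence and duration of invasive mechanical ventilation".

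**The concern.** A free-day count piles up at its two ends. Everyone who survives and never needs the support scores 28, and the deaths score 0. The median looks only at the middle-ranked participant. While more than half of each arm sits at 28, both medians are 28 and their difference is 0, however many deaths or treated survivors separate the arms below the middle.

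The risk is a published line reading 0 (95% CI 0 to 0). It looks like a very precise finding of no effect, when it carries no information on the effect beyond the fact that more than half of each arm scored 28.

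**Working it through.** **Inputs from the protocol**
- Mortality, low figure: section 6, preliminary data, reports that "in-hospital mortality was 8"% among 82 patients with septic shock.
- Mortality, high figure: section 6 gives an "overall in-hospital mortality rate of 18%, and 22% in the subgroup with shock" among ICU patients. Both are in-hospital figures, used here in place of 28-day mortality.
- Arm size: section 13.1 plans for 950 evaluable participants, so 475 per arm. That figure reproduces: 2 × (1.960 + 1.282)² × 31² / 7² gives 413 per arm after rounding up; 826 × 1.15 = 949.9, or 950; 950 / 0.95 = 1000. The protocol states no figure for the free-day outcomes.

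**Assumptions**
- Scoring: 28 if alive and never supported, 0 if dead, 28 minus days of support otherwise.
- Renal replacement in 6–12% of participants; ventilation in 15–40%.
- Duration of support exponential with mean 6 days.
- Percentile bootstrap interval for the median difference; no site effect simulated.

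**Step 1: when the median leaves 28.** With mortality m and a share u of survivors supported, the share at 28 is (1 − m)(1 − u). The median falls below 28 only if this drops under one half, that is, if u exceeds (0.5 − m) / (1 − m).

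| Mortality | Share of survivors who must be supported |
|---|---|
| 8% | 0.42 / 0.92 = 45.7% |
| 15% | 0.35 / 0.85 = 41.2% |
| 18% | 0.32 / 0.82 = 39.0% |
| 22% | 0.28 / 0.78 = 35.9% |

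Sampling variation does little to rescue it. In an arm of 475, the binomial chance that at least 238 are dead or supported is about 5 in a million when the true share is 40%, 0.001 at 43% and 0.014 at 45%.

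**Step 2: renal-replacement-free days.** The share of an arm at 28 runs from 0.78 × 0.88 = 69% (mortality 22%, use 12%) to 0.92 × 0.94 = 86% (mortality 8%, use 6%). That is far above one half throughout.

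| Deaths | Renal replacement | Result exactly 0 (0 to 0) | Mean difference | Rank-sum power |
|---|---|---|---|---|
| 22% v 18% | 12% v 6% | 100% of trials | 1.3 days | 71% |
| 18% v 11% | 12% v 8% | 100% | 2.1 days | about 95% |
| 22% v 8% | 12% v 12% | 100% | 3.8 days | 100% |

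**Step 3: ventilator-free days.** Here the answer turns on the assumed ventilation rate.

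| Deaths | Ventilated | Both medians 28 | Exactly 0 (0 to 0) | Rank-sum power |
|---|---|---|---|---|
| 15% v 10% | 25% v 15% | 100% | 100% | 98% |
| 22% v 18% | 30% v 20% | 98.5% | 54% | 85% |
| 18% v 15% | 35% v 25% | 93.5% | 31.5% | 83% |
| 22% v 18% | 40% v 30% | 9.5% | 0% | 87% |

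**Step 4: vasopressor-free days.** With 85% use and 15% mortality (both assumed), only 0.85 × 0.15 = 12.8% of an arm sits at 28. With durations set from the pilot's medians of 33 and 20 hours (section 6), both medians were at 28 in none of the simulated trials.

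**The case against.** A good deal of the opposing case stands.

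- **The assignment is by elimination.** Section 13.2 does not name the free-day outcomes, and a detailed analysis plan is promised. But the protocol does state a method for outcomes of this kind. A plan that follows it inherits the problem, so this is a poor choice that has been fixed in the text, not a detail left open.
- **No ventilation rate is given.** A reader might infer that ventilator-free days must also return zero whatever the treatment does. The documents do not support that. Near the threshold the median is unstable, and above it the median moves.
- **Vasopressor-free days.** A reader might count these as a third outcome fixed at zero. They are not: most participants are expected to receive a vasopressor, so the median lies below 28.
- **Real effects are not simply hidden.** All-cause mortality and time to death are secondary outcomes in their own right, and the incidence and duration of each support are tertiary outcomes. Much of the rank-sum power above comes from the assumed mortality gap, which a comparison of deaths would often detect alone. For 18% v 11% with 475 per arm, 0.07 / √(0.18 × 0.82 / 475 + 0.11 × 0.89 / 475) = 3.08, and 3.08 − 1.96 = 1.12, about 87% power.
- **The simulation is not the planned model.** It leaves out the site effect, and section 13.2 does not fix the interval method. Another method could give an interval with some width, but it would still surround a difference between two values at the ceiling.

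These points narrow the finding and lower its weight. They do not make a median difference informative for renal-replacement-free days.

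**Conclusion.** The point holds for renal-replacement-free days. Across the assumed 6–12% use and the protocol's 8–22% mortality, the prescribed summary is 0 (0 to 0), even where the arms differ by 3.8 mean free-days. To escape this, about 36% to 46% of survivors would have to receive renal replacement, which is implausible.

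For ventilator-free days it is conditional. The result is degenerate if the ventilated share of survivors is well under 36–46%, unstable close to that range, and not degenerate above it. It does not hold for vasopressor-free days.

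All of this rests on the usual scoring, which the protocol does not state for these outcomes, on support rates that it does not give, and on in-hospital mortality as a stand-in for 28-day mortality.

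The consequence is one secondary outcome, possibly two, that would tell the reader nothing. This point does not affect the primary outcome or the sample size. The change should be made, but it is not a condition for the trial's validity.

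**What to change.** In section 13.2, take renal-replacement-free and ventilator-free days out of the quantile-regression rule. Analyse them with a proportional-odds or other rank-based model with a site effect, and report the difference in mean free-days with a bootstrap confidence interval beside it. Vasopressor-free days may be handled the same way for consistency, though the finding does not require it. State in the same place how deaths and never-supported survivors are scored. Quantile regression can stay for outcomes whose median lies away from a boundary, such as length of stay.

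The cost is a sentence or two and a standard model, with no new data and no extra participants. A common odds ratio is harder to read than a difference in days; the mean difference makes up for that. The change should be settled before anyone sees results by arm.

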# **10. STUDY PROCEDURES**

## **10.1 Randomisation**

Randomisation will be performed by the site investigator, research coordinator or delegated staff at each site. This will occur through a dedicated, secure, password-protected, encrypted website which is available 24 hours, 7 days a week. Patients will be randomised using computer-generated, block randomisation sequence with variable block sizes and stratified by participating centre. Patients will be assigned in a 1:1 ratio to either: the Vasopressors arm or Fluids arm. Upon randomisation, the website will assign a unique patient study number.

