### **2. Baseline (immediately prior to randomisation)**

- Baseline demographics (age, sex, weight, ethnicity)
- Suspected source of infection
- Usual residence
- Pre-existing comorbidities (as defined by the Charlson Comorbidity Index Score)
- Physiological and laboratory variables, if available
- Date, time and name of first IV antimicrobial agent
- IV fluids administered prior to randomisation (volume and type)
- Severity of illness and organ failure scores (APACHE II, SOFA)

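### The adjusted sensitivity analysis picks its covariates by baseline tests at p<0.2, which selects on chance; a short prognostic list fixed in advance should replace it

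*Protocol*

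**What the plan says.** Protocol section 13.2 analyses DAOH-D90 by quantile regression and binary outcomes by logistic regression, with site as a random effect throughout. Its only adjustment for patient characteristics is conditional: where a baseline difference reaches p<0.2, it "is observed between treatment arms, sensitivity analysis will be performed adjusting for imbalanced variables". It does not say which variables are tested or by which test.

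Allocation is random: "Patients will be assigned in a 1:1 ratio to either: the Vasopressors arm or Fluids arm" (section 10.1), stratified by centre and by no patient characteristic.

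Section 12.2 lists the baseline data that will be collected in any case: age, sex, weight, ethnicity, usual residence, Charlson comorbidities, physiological and laboratory values where available, and "Severity of illness and organ failure scores (APACHE II, SOFA"). A lactate above 2.0 mmol/L is an inclusion criterion (section 9.3). Section 13.3 already treats age, baseline lactate and APACHE II as important enough to define subgroups.

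**The concern.** After valid randomisation, any baseline difference between arms is due to chance. A p-value for it says nothing about whether the variable predicts outcome, yet prediction is what makes a covariate worth adjusting for. The rule therefore has three faults.

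- It can adjust for a variable that has no bearing on DAOH-D90.
- It will usually leave out any given strong predictor.
- It leaves the content of the model open until the arms have been compared.

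What is at stake is the usefulness of the adjusted analysis. Readers will look to it to see whether the result holds once patient severity is allowed for, and under this rule it may not contain severity at all. The baseline data for a better analysis are already being gathered.

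**Working it through.** **1. The plan's own sample size.** Inputs from section 13.1: "the mean (standard deviation) of DAOH-D90 was 60(31"), a 7-day difference ("Assuming a clinically important increase of 7 days in the vasopressors arm"), 90% power, and a type I error of 0.05 (two-sided assumed, since sidedness is not stated).

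- Per arm: 2 × (1.960 + 1.282)² × 31² / 7² ≈ 412.2, rounded up to 413; total 826.
- With the stated 15% inflation: 826 × 1.15 = 949.9, so 950.
- With 5% drop-out: 950 / 0.95 = 1000.

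Both stated figures reproduce, and neither uses covariate adjustment. Power at 950 (effective size 950 / 1.15 ≈ 826) is 90.1%.

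**2. What the trigger selects.** Under randomisation a baseline p-value is below 0.2 with probability about 0.20. Any named variable, such as APACHE II, is thus adjusted for about 20% of the time and left out about 80% of the time. For k independent variables, the expected number of flags is 0.2k and the probability of at least one is 1 − 0.8^k. The protocol does not give k, so a range is shown:

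| k | Expected flags | P(at least one) |
|---|---|---|
| 5 | 1 | 67% |
| 10 | 2 | 89% |
| 15 | 3 | 96% (0.9648) |
| 20 | 4 | 99% |

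The baseline variables overlap (age contributes to severity scores, for example), so the last column is a guide. The 20% for each single variable does not need independence.

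**3. Precision available from a prognostic list.** Let R² be the share of DAOH-D90 variance explained by the covariates. The documents give no value, so it is assumed. In a linear model the standard error is multiplied by √(1 − R²).

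| R² | Fall in standard error | Power at 950 |
|---|---|---|
| 0.05 | 2.5% | 91.5% |
| 0.10 | 5.1% | 92.8% |
| 0.15 | 7.8% | 94.1% |
| 0.20 | 10.6% | 95.2% |

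**4. Does this carry over to medians?** A small simulation used a DAOH-like outcome with deaths set to zero, no treatment effect, one covariate, 950 patients and 600 runs per scenario. It gave these standard deviations of the estimated median difference, in days:

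| Outcome R² | Never adjusted | Always adjusted | Adjusted only if p<0.2 |
|---|---|---|---|
| about 0.08 | 1.46 | 1.35 | 1.42 |
| about 0.19 | 1.59 | 1.43 | 1.54 |

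The covariate was selected in 20% to 22% of runs. Always adjusting cut the standard deviation by about 8% and 10%, in line with step 3, and the p<0.2 rule lost most of that gain. With one invented covariate and 600 runs, this supports the direction and rough size only; a few of the median fits also stopped at their iteration limit.

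**The case against.** The strongest reply is that the rule governs a sensitivity analysis and nothing else. That is correct. A reader might infer that the main result is biased or that the trial loses its stated power. The documents do not support this: the primary model in section 13.2 does not use the rule, and section 13.1 reaches its sample size without adjustment.

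A second reply is that the lost precision comes from having no prognostic covariates in the model, not from the p<0.2 rule, so deleting the rule alone recovers nothing. This also stands. Nor is the lack of a covariate list in itself a fault, because lists are commonly left to the statistical analysis plan. The fault is the selection rule that the protocol fixes.

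A third reply is that the rule has a sensible purpose: to check whether observed imbalances explain the result. At 1000 patients, p = 0.2 corresponds to a standardised difference of 1.28 × 2/√1000 = 0.081. In a linear approximation, one unflagged covariate with R² of 0.10 to 0.20 shifts the estimate by at most 0.081 × 31 × √R², or 0.8 to 1.1 days, against a 7-day target. So no single omitted predictor can distort the result much, although several could add up. This limits the harm, but it does not make the rule informative: a flagged variable unrelated to outcome triggers an adjustment that changes almost nothing, while an unflagged predictor that does move the estimate is ignored.

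A reader might also take 1/(1 − R²), which is 1.11 to 1.25 here, to mean 11% to 25% more patients at no cost. That is too strong. R² is assumed, the formula belongs to linear models of means, and it does not apply to logistic regression for mortality, where adjustment changes the odds ratio being estimated and does not shrink its standard error in this way.

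**Conclusion.** The point holds, within limits. Section 13.2 fixes a covariate-selection rule that works on chance: about a 20% probability of inclusion for any variable, whatever its prognostic value, in a model that cannot be known before the arms are compared. This rests only on randomisation.

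The primary estimate, its type I error and the stated 90% power are unaffected. The cost is a sensitivity analysis that tells the reader little, plus a modest forgone gain in precision. The 5% to 11% fall in standard error depends on an assumed R² of 0.10 to 0.20 and a linear approximation, which is only a guide for median regression. The illustration of 3 flags and a 96% chance of at least one assumes 15 independent variables. The change is worth making, but the trial's main conclusion does not hang on it.

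**What to change.** In section 13.2, delete the p<0.2 trigger. Replace it with one adjusted analysis of DAOH-D90 and of 90-day mortality that:

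- uses a short covariate list chosen for prognosis and fixed before any data by arm are seen, for example age, APACHE II, baseline lactate and Charlson score, together with site;
- is applied whatever the observed balance;
- is labelled as primary or as sensitivity (precision improves only in the analysis that carries the covariates);
- states how missing baseline values are handled.

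The named covariates are examples; the documents do not rank predictors of DAOH-D90, so the investigators should settle the list.

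The cost is a few sentences in section 13.2, matched in the statistical analysis plan, with no new data collection. There are two small downsides. Adjusted median differences and odds ratios are conditional estimates and should be described as such. Some values may also need imputation, because section 12.2 collects physiological and laboratory data only where available and section 10.6 requires no extra tests. Lactate should be nearly complete, since eligibility depends on it.
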